#### Allocation and Blinding

Because hospitals were preassigned to their respective study arms, no individual-level randomization will be implemented. The study will be conducted as a single-blinded trial whereby participants will not be informed of their allocation to either the intervention or control group and will instead be informed that they will receive “health education material,” as stated in the patient information sheet. In addition, researchers responsible for data analysis will remain blinded to group assignment until all data have been cleaned and finalized to minimize analysis-related bias.

#### Intervention (Intervention Arm)

Participants assigned to the intervention hospitals will receive the *DemensiaKITA* mHealth app. The app will be installed directly by the research team to prevent unauthorized sharing. Participants may access the app freely during the study period.

### DemensiaKITA Mobile Health App Intervention

#### Overview

The *DemensiaKITA* app is an offline mobile app prototype developed by a team of researchers from Universiti Teknologi MARA, Malaysia, and the Canadian University of Dubai (Figure 3). The app has been granted copyright protection under Universiti Teknologi MARA. It provides essential information on dementia and dementia care, facilitates easy access to nearby health services, optimizes the use of available local resources, and enhances caregiving skills. The app features appropriate and relevant content tailored for the Malaysian context, using the national language (Bahasa Malaysia) as the interface, specifically designed for dementia caregivers in Malaysia (Figure 3 and Textboxes3  4) [12].

**Figure 3. F3:**
[figure not shown]
Features of *DemensiaKITA* mobile health app.

Textbox 3.Additional features of the *DemensiaKITA* app (support functions to reduce caregiver burden).Stress and emotional management: Resources to help caregivers cope with stress and emotional challenges, potentially reducing their emotional burden.Daily motivation: Encouragement and inspiration to support caregivers in their daily routines, potentially reducing their emotional and social burdens.Support group: Access to online and in-person support groups, helping caregivers connect with others and reduce feelings of isolation, potentially reducing emotional and social burdens.List of available services (including health services, nongovernment organizations, daycare, and nursing home): A comprehensive list of available services, enabling caregivers to find the support they need and potentially reduce their physical burden by facilitating access to care.List of available welfare aid: Details on available financial assistance and welfare programs to help alleviate the financial burden of caregiving.

Textbox 4.Basic features of the *DemensiaKITA* app (information and guidance on dementia care).The *DemensiaKITA* app aims to improve the caregivers’ knowledge, attitudes, and practices in taking care of people living with dementia. It provides information and guidance on various aspects of dementia care:Regarding dementiaEmotional disturbance of people living with dementiaBasic care of people living with dementiaDietary care of people living with dementiaOral exercise for people living with dementiaBasic exercise for people living with dementiaPhysical and memory rehabilitation

#### Engagement and Adherence Monitoring

To promote engagement with the *DemensiaKITA* app, caregivers in the intervention group will receive a brief, standardized orientation on the app features at enrollment. Thereafter, the research team will send scheduled reminders via WhatsApp or SMS text messaging to encourage continued use of the app and completion of follow-up assessments. Reminders will be sent once weekly during the first month and every 2 weeks thereafter until the 3-month follow-up.

#### Comparator (Control Arm)

Caregivers in the control arm will receive standard Ministry of Health (MOH) dementia educational materials, which are the dementia leaflets and video. These materials will be explained in detail during the baseline session to ensure consistent educational exposure and engagement comparable to that provided in the intervention arm [42].

#### Dementia Leaflets and Video

The dementia leaflets and video provided by the MOH Malaysia offer essential information on the nature of dementia, its common symptoms, and the groups at higher risk (Figure 4). They emphasize the importance of early detection and timely diagnosis, describe the available assessments conducted in clinics and hospitals, and outline practical steps to help maintain cognitive and physical well-being. The materials also highlight key measures that may reduce dementia risk, including mentally stimulating activities, regular exercise, healthy lifestyle practices, and effective management of chronic illnesses. In addition, they provide guidance on daily care, safety, behavioral management, and available support resources to assist people living with dementia and their caregivers [42].

**Figure 4. F4:**
[figure not shown]
Ministry of Health Malaysia leaflets and video.

### Data Collection Method and Study Tool

Data will be collected using a validated self-administered questionnaire at 3 time points: baseline, 1 month postintervention, and 3 months postintervention. The study tool is a Malay-translated and validated questionnaire assessing KAP and burden levels. Participants in the intervention group will have access to the mobile app 2 weeks before the study starts to get familiar with it.

Before the study begins, all participants will be informed of the study objectives, procedures, potential risks, and benefits and will provide informed consent. Participation is voluntary, and participants may withdraw at any time without penalty. To help keep participants engaged, reminders will be sent via WhatsApp or email throughout the study. These reminders will also check on app use for the intervention group and encourage continued participation until 3 months postintervention.

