**Results:**

Recruitment and baseline data collection are underway. Recruitment for Phase 1 (instrument validation) occurred from December 2024 until July 2025. It is expected to produce valid and reliable Malay versions of KAP and burden instruments. Recruitment for the Phase 2 NRCT will occur from August 2025 until February 2026. The first follow-up data collection for Phase 2 will occur 1 month after baseline, and the second and final follow-up will occur at 3 months. Data analysis has not yet begun. Phase 2 is expected to show significant improvements in dementia KAP and reduced caregiver burden in the intervention group compared to controls. This study was conducted without any specific external financial support or grants from any public, commercial, or not-for-profit funding agencies. The study findings are expected to be published in December 2026.

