### Phase 2: Effectiveness of the *DemensiaKITA* mHealth App

#### Overview

In Phase 2, the research assesses the effectiveness of the *DemensiaKITA* mHealth app intervention among dementia caregivers in Selangor, Malaysia. This phase uses an NRCT with 2 parallel arms (intervention and control) and a 1:1 allocation ratio. The study includes 3 assessment points: baseline (T0), 1 month (T1), and 3 months (T2). The intervention period spans from August 2025 to February 2026. Participants will be blinded to group allocation (single-blinded). Hospital-level allocation is applied to minimize contamination (Figure 2). Eligibility criteria for Phase 2 are given in Textbox 2.

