#### Inferential and Longitudinal Analysis

All analyses will be conducted using a 2-sided significance level of *α*=.05. Descriptive statistics will summarize sociodemographic and caregiving characteristics by study arm [46]. Categorical variables will be presented as frequencies and percentages, and continuous variables as means and SDs or medians and IQRs, as appropriate. Baseline comparability between the intervention and control groups will be examined using chi-square tests for categorical variables and independent *t* tests (or nonparametric equivalents) for continuous variables [46,47].

The primary effectiveness analysis will use generalized estimating equations models to compare changes in knowledge, attitude, practice, and burden scores between the intervention and control groups over time (baseline, 1 mo, and 3 mo). For each outcome, a GEE model with an appropriate link function and working correlation structure will be fitted, including fixed effects for group (intervention vs control), time, and the group-by-time interaction. The group-by-time interaction term will be interpreted as the main estimate of the intervention effect. To account for potential confounding due to nonrandom allocation, the models will adjust for prespecified baseline covariates (age, sex, and relationship with the people living with dementia, caregiving duration, and baseline score of the corresponding outcome). Robust standard errors will be reported [21,48].

Effect sizes (Cohen *d* for between-group differences in mean change) will be calculated to quantify the magnitude of the intervention effect, in addition to *P* values and 95% CIs [21,48].

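### Only the intervention arm has a 2-week head start with the app, and nothing in the protocol places the baseline questionnaire ahead of it

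*Protocol article*

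**What the plan says.** Timing of exposure and measurement is described in several places.

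- Data Collection Method and Study Tool, app access: "Participants in the intervention group will have access to the mobile app 2 weeks before the study starts to get familiar with it". No matching lead-in is given to controls.
- The same section, measurement times: "baseline, 1 month postintervention, and 3 months postintervention". The Phase 2 Overview labels the baseline assessment T0 and makes it the first of three.
- Engagement and Adherence Monitoring: "caregivers in the intervention group will receive a brief, standardized orientation on the app features at enrollment".
- Comparator (Control Arm), on the leaflets and video: "These materials will be explained in detail during the baseline session to ensure consistent educational exposure". That section adds that engagement is meant to match the intervention arm's.
- Abstract, Results: "The first follow-up data collection for Phase 2 will occur 1 month after baseline".
- Inferential and Longitudinal Analysis: "The group-by-time interaction term will be interpreted as the main estimate of the intervention effect". The model also adjusts for the baseline score of each outcome, and Cohen d is calculated on mean change.

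No section says whether the T0 questionnaire is completed before or after the app becomes available.

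**The concern.** Familiarisation with this app is treatment. The app delivers information and guidance intended to raise knowledge, attitudes and practices, and no restricted or content-free version is described for the lead-in. Knowledge, the outcome used for the sample size, is the one most likely to move as soon as the content is read.

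Every effect measure is anchored on T0. If intervention caregivers have already used the app for 2 weeks by then, part of what the trial wants to measure is counted as baseline.

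This matters more here than in a randomised trial. Hospitals were assigned without randomisation, and the Study Design section relies on baseline comparison and on GEE adjustment for baseline imbalance as two of its four safeguards. With a post-exposure T0 in one arm, a pre-existing site difference in outcome scores could not be told apart from an early app effect.

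**Working it through.** **1. Order of events.** Take 1 month as about 4 weeks and 3 months as about 13 weeks. Weeks of exposure to study material at T0 / T1 / T2:

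| Reading | App arm | Control arm |
|---|---|---|
| A. T0 when the study starts, after the lead-in | 2 / 6 / 15 | 0 / 4 / 13 |
| B1. T0 before the lead-in, follow-up counted from T0 | 0 / 4 / 13 | 0 / 4 / 13 |
| B2. T0 before the lead-in, follow-up counted from study start, control baseline session at study start | 0 / 6 / 15 | 0 / 4 / 13 |

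Reading A follows most directly from the text: access precedes the study, and T0 is its first assessment. B1 is sound, but it requires T0 to fall before the point the protocol calls the start of the study. B2 has a clean baseline but unequal exposure, which could favour the app.

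**2. Effect on the estimate under Reading A.** Let E be the app-versus-control difference at follow-up that would be seen against an unexposed baseline, and a the part already gained by T0. The contrast in change from T0 is E − a. With a = f × E, this is E(1 − f). The baseline score is a single fixed value per caregiver, so as a covariate it shifts level and not change over time. It is also itself raised by a in one arm only, so adjusting for it cannot restore a.

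**3. The plan's own sample size.** Inputs from Sample Size Calculation: difference 1.69, SDs 2.53 and 2.76, two-sided alpha 0.05, power 0.80, attrition 30%.

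- Variance sum: 2.53² + 2.76² = 6.4009 + 7.6176 = 14.0185
- n = 14.0185 × (1.96 + 0.842)² / 1.69² = 38.54, rounded up to 39 per group
- 38.54 × 1.30 = 50.1, stated as 50 per group

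The plan's figures reproduce.

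**4. Illustration of the loss.** The share f is not in the documents; 10% to 50% is an assumed range. Power = Φ(1.69(1 − f)/SE − 1.96), where SE = √(14.0185/n). This gives SE = 0.600 at n = 39 and 0.633 at n = 35 (50 per arm less 30%).

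| f | Remaining difference | Power, 39 per arm | Power, 35 per arm | n per arm for 80% power |
|---|---|---|---|---|
| 0 | 1.69 | 80.5% | 76% | 39 |
| 10% | 1.52 | 72% | 67% | 48 |
| 25% | 1.27 | 56% | 52% | 69 |
| 50% | 0.85 | 29% | 27% | 155 |

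These are powers for a comparison of two independent means, as in the plan's calculation. They are not the power of the adjusted GEE interaction, which depends on a within-person correlation that the protocol does not give.

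**The case against.** The strongest reply is that the order is inferred. The start of the study is never defined, and the Phase 2 flowchart, which might show the order, is not visible in the text at hand. Consent is obtained beforehand, orientation takes place at enrollment, and the control session is meant to be comparable. All of this fits T0 at enrollment, followed by familiarisation and then the timed period. Orientation at enrollment and a 2-week lead-in are compatible if enrollment comes 2 weeks before the start. Counting follow-up from baseline or from the intervention may be no more than a difference in wording.

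This stands as far as it goes. A reader might infer that baseline is certainly contaminated and the trial biased towards no effect. The documents do not support that as settled fact: a clean T0 is not excluded, bias towards no effect needs both Reading A and some benefit within 2 weeks, and Reading B2 could bias in the app's favour. A reader might also infer that the whole baseline comparison is invalid. It is not. Age, sex, relationship and caregiving duration are unaffected by app access; only the T0 outcome scores could be.

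The reply does not remove the point. This is not a detail merely left to a fuller document: the article positively states a lead-in for one arm, and its timing statements do not fix a common time zero.

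**Conclusion.** The point holds as a conditional one. Following the text on its plain reading gives T0 outcome scores that are post-exposure in the intervention arm only. The group-by-time estimate and Cohen d on change then lose whatever was gained early, and baseline adjustment does not repair this. If T0 precedes the lead-in, baseline is sound; what remains is an undefined clock and possibly about 2 weeks of unequal exposure at T1 and T2.

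The size of any bias cannot be derived from the documents. The drop from about 80% to 56% or 29% power at 39 per arm (76% to 52% or 27% at 35 per arm) illustrates assumed early shares of 25% and 50%, and no more. Because the main estimate rests on T0, the order should be settled before data are collected.

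**What to change.** State that in both arms the T0 questionnaire is completed after consent and before any study material is given: before the app is installed or accessible in the intervention arm, and before the leaflets and video are explained in the control arm. Count T1 and T2 from the same event in both arms. Reconcile the statements in the Abstract (Results), Engagement and Adherence Monitoring, Comparator (Control Arm), and Data Collection Method and Study Tool.

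The cost is the order of steps at the enrolment visit and a few sentences of text, with no extra visits or participants. The article reports that Phase 2 had not started at submission. If enrolment has since begun, document the order actually used at each site, so that the T0 scores can be interpreted correctly.

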### Sample Size Calculation

The sample size for Phase 2 was calculated for comparison of 2 independent means (intervention vs control) assuming equal group sizes, a 2-sided test with a significance level of *α*=.05, and power (1−β)=0.80. The calculation followed the method described by Rosner [43] and Turnbull et al [44]. The required sample size per group was obtained using the formula:

$$n=\frac{(\sigma_{1}^{2}+\sigma_{2}^{2})(Z_{1-\alpha /2}+Z_{1-\beta }{)}^{2}}{\Delta^{2}}$$

where $\sigma_{1}$ and $\sigma_{2}$ are the SDs in the 2 groups, $Z_{1-\alpha /2}$ is the standard normal deviate at the 5% (1.96) significance level, $Z_{1-\beta }$ is the standard normal deviate for 80% (0.84) power, and Δ is the expected mean difference between the groups.

Based on Turnbull et al [44], an expected mean difference in knowledge scores of 1.69 was used, with SDs of 2.53 and 2.76, respectively. Substituting these values:

$$n=\frac{(2.53^{2}+2.76^{2})(1.96+0.842{)}^{2}}{1.69^{2}}\approx 38.5$$

Thus, approximately 39 participants are required per group. To account for an anticipated 30% attrition rate, the sample size was inflated:

$$n_{\text{adjusted}}=38.5\times 1.30\approx 50$$

Accordingly, 50 participants will be recruited into each arm (intervention and control), giving a total sample size of 100 caregivers.

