## Methods

### Study Design

This study consists of 2 sequential phases: (1) adaptation, translation, and validation of KAP and burden-related instruments, and (2) evaluation of the *DemensiaKITA* mHealth intervention via a single-blinded NRCT. The NRCT design was selected due to operational and ethical constraints within participating hospitals. Caregivers are tied to specific clinics based on people living with dementia follow-up, and redistributing them across hospitals for randomization would disrupt continuity of care. Cluster randomization was not feasible due to small eligible populations within each site. Individual randomization within the same clinic would introduce high contamination risks, as caregivers frequently interact and could share intervention materials.

To mitigate potential biases inherent in nonrandom allocation, the study incorporates several methodological safeguards: (1) standardized inclusion and exclusion criteria across all sites; (2) selection of hospitals with comparable geriatric services; (3) baseline comparison of groups; and (4) longitudinal analyses using generalized estimating equations (GEE) to adjust for baseline imbalances and repeated measurements [20,21]. This pragmatic design reflects real-world implementation conditions while preserving internal validity.

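### The 80% power and the caregiver-level standard errors hold only if the four allocated hospitals do not differ in change over time; the protocol neither states nor tests this condition

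*Protocol article*

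**What the plan says.** On allocation, the Phase 2 Overview says: "Hospital-level allocation is applied to minimize contamination". Study Settings names two hospitals for each arm. Allocation and Blinding confirms that hospitals were assigned in advance and that caregivers are not randomized individually. Study Design explains the choice: "Cluster randomization was not feasible due to small eligible populations within each site".

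On size, Sample Size Calculation says: "The sample size for Phase 2 was calculated for comparison of 2 independent means (intervention vs control) assuming equal group sizes". It uses "a 2-sided test with a significance level of *α*=.05, and power (1−β)=0.80", and "an expected mean difference in knowledge scores of 1.69 was used, with SDs of 2.53 and 2.76, respectively". It concludes that "approximately 39 participants are required per group". The only later adjustment is for dropout: "To account for an anticipated 30% attrition rate, the sample size was inflated", giving 50 per arm.

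On analysis, Inferential and Longitudinal Analysis specifies a GEE for each outcome, "including fixed effects for group (intervention vs control), time, and the group-by-time interaction". The model also has age, sex, relationship, caregiving duration and the baseline score as covariates. Robust standard errors are promised, but the unit on which they are clustered is not named. Study Design gives the purpose of the GEE as correcting baseline differences and handling repeated measures. Correlation between caregivers at the same hospital is not mentioned anywhere.

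**The concern.** The unit of allocation is the hospital, while the sample size formula treats the caregiver as an independent unit. Caregivers at one clinic share staff, local education and referral patterns, so their changes over three months may be more alike than those of caregivers at different clinics. If so, 39 caregivers per arm carry less information than 39 independent ones. A standard error built at caregiver level then understates the uncertainty in the group-by-time effect.

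That effect is the protocol's main estimate for all four outcomes, and the Discussion proposes using the findings to inform national policy. The confidence interval and P value attached to it therefore matter. Study Design sets cluster randomization aside on feasibility grounds, but assigning hospitals without randomizing them carries the same clustering. None of the four safeguards listed there addresses it.

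**Working it through.** **Inputs from Sample Size Calculation.** Difference 1.69; SDs 2.53 and 2.76; multipliers 1.96 and 0.842; 39 evaluable and 50 recruited per arm; 30% attrition. Study Settings gives two hospitals per arm.

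**Assumed, because the protocol does not give them.** ICC of change 0.01, 0.02 and 0.05; equal recruitment per hospital; the stated SDs apply to the contrast tested.

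**Step 1: reproduce the plan's figure.** Sum of variances = 2.53² + 2.76² = 14.0185. n = 14.0185 × (1.96 + 0.842)² / 1.69² = 38.54, so 39 per arm. 38.54 × 1.30 = 50.1, so 50 per arm. Both figures reproduce under independence. Power at 39 per arm is Φ(1.69/√(14.0185/39) − 1.96) = Φ(2.819 − 1.96) = 80.5%.

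**Step 2: add clustering.** With m = n/2 caregivers per hospital:
- Design effect DE = 1 + (m − 1) × ICC
- Power = Φ(1.69/√(14.0185 × DE/n) − 1.96)
- Type I error of a nominal 5% test that ignores hospital = 2Φ(−1.96/√DE)

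Example with n = 39 and ICC 0.02: DE = 1 + 18.5 × 0.02 = 1.37. SE = √(14.0185 × 1.37/39) = 0.702. Power = Φ(2.408 − 1.96) = 67.3%. Type I error = 2Φ(−1.96/1.170) = 9.4%.

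| Evaluable per arm | ICC | DE | Power | Type I error | Naive SE / true SE |
|---|---|---|---|---|---|
| 39 | 0 | 1.00 | 80.5% | 5.0% | 1.00 |
| 39 | 0.01 | 1.19 | 73.5% | 7.2% | 0.92 |
| 39 | 0.02 | 1.37 | 67.3% | 9.4% | 0.85 |
| 39 | 0.05 | 1.93 | 52.9% | 15.8% | 0.72 |
| 35 | 0 | 1.00 | 76.1% | 5.0% | 1.00 |
| 35 | 0.01 | 1.17 | 69.6% | 6.9% | 0.93 |
| 35 | 0.02 | 1.33 | 63.9% | 8.9% | 0.87 |
| 35 | 0.05 | 1.83 | 50.7% | 14.7% | 0.74 |
| 50 | 0 | 1.00 | 89.1% | 5.0% | 1.00 |
| 50 | 0.01 | 1.24 | 81.8% | 7.8% | 0.90 |
| 50 | 0.02 | 1.48 | 74.7% | 10.7% | 0.82 |
| 50 | 0.05 | 2.20 | 57.6% | 18.6% | 0.67 |

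The rows for 35 are 50 less 30%. Their 76% at ICC 0 is not a clustering effect. It arises because multiplying by 1.30 does not offset a 30% loss (38.5/0.70 = 55). Clustering accounts only for the fall from 76% to 70%, 64% and 51%.

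**Step 3: can more caregivers compensate?** With two hospitals per arm, n/DE approaches 2/ICC as n grows. It must reach 38.5 for 80% power, so that power is out of reach once the ICC exceeds 2/38.5 ≈ 0.052.

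**Step 4: analysis at hospital level.** Four hospital summaries less two arm means leave 2 degrees of freedom, with a critical t of 4.30. From the noncentral t distribution at ICC 0, power is 33% with 35 per arm, 35% with 39 and 42% with 50.

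**The case against.** **The main effect is a contrast in change.** The model tests group by time and adjusts for baseline, so stable differences between hospitals largely cancel. What matters is the ICC of change, which may be small. At 0.01 the type I error is only about 7%, and with all 50 caregivers per arm retained, power is still about 82%. This stands. It makes the claim conditional, but the direction is the same for any positive ICC.

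**The unit for the robust standard errors is not named.** An analysis plan could specify the hospital. That also stands: caregiver-level clustering is the natural reading of Study Design, not an explicit statement. Neither reading rescues the inference, though, since a sandwich estimator built on four clusters is unreliable.

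**The SDs may not match the contrast.** The protocol does not say whether they describe raw scores or change. If they describe raw scores, baseline adjustment could move the residual variance either way. The figures are therefore illustrations, not a corrected power.

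**Stronger readings a reader might infer.** One is that hospital-specific change is completely aliased with arm. It is not: two hospitals per arm leave 2 degrees of freedom for differences within an arm. Another is that every difference in drift between hospitals is counted as an app effect. Only a difference between the averages of the two pairs shifts the estimate, and the listed covariates may absorb part of any difference in case mix. A third is that the power and type I error are definitely wrong. Without an ICC of change, the documents support that only conditionally.

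**The limitations section partly covers this.** It acknowledges selection bias and limited generalizability, but not clustering.

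**Conclusion.** The point holds in conditional form. The stated 80% power rests on an independence assumption that the allocation unit does not support, and the model as described has no term for hospital. If the ICC of change is between 0.01 and 0.05, power at the protocol's own 39 per arm is about 73.5% down to 53%, and the caregiver-level test has a type I error of about 7% to 16%. These figures assume equal recruitment per hospital, the protocol's SDs and the normal approximation. If all 50 per arm are retained, the power range is 82% to 58%; with 35 completers it is 70% to 51%, starting from 76% at ICC 0.

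Arm is a contrast between two pairs of hospitals with 2 degrees of freedom for error. Statistical adjustment within this design therefore cannot distinguish a pair-level difference in average drift from the app's effect. Adding hospital as a full fixed effect would not help, because hospital is nested in arm. The caregiver-level P value and confidence interval should be read as applying to these four hospitals.

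**What to change.** - **Sample Size Calculation:** say that the 80% power assumes no between-hospital variation in change. Give the power for ICC 0.01 to 0.05 beside it, labelled as an assumed range.
- **Inferential and Longitudinal Analysis, and the sensitivity analysis section:** name the unit on which the robust standard errors are clustered. Prespecify reporting of the adjusted mean change for each of the four hospitals. A hospital-level analysis with 2 degrees of freedom can be added as optional, but it should be labelled descriptive, because its power is only about 33% to 42% even at ICC 0 and it cannot confirm or refute the main result.
- **Interpretation and limitations:** state that the caregiver-level P values and confidence intervals are conditional on these four hospitals, and limit the effectiveness conclusion accordingly.

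The cost is wording and one small table, plus a less favourable power statement and a narrower conclusion. No extra participants or hospitals are needed. The article reports that Phase 2 had not started at submission and that analysis had not begun, so these changes could still have been prespecified at that point.

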#### Knowledge

Caregiver knowledge will be assessed using the DKAT-2, developed by Toye and colleagues [22] at Curtin University. The DKAT-2 consists of 21 items with Yes/No/Don’t Know response options and measures understanding of the dementia trajectory and evidence-based care approaches. Each item is scored as correct or incorrect, with “Don’t Know” categorized as incorrect. Total scores reflect overall knowledge, with higher scores indicating greater understanding of dementia care. The DKAT-2 demonstrates strong psychometric performance, including high internal consistency (Cronbach *α*=0.79), supporting its use in evaluating caregiver education and guiding patient-centered interventions [22].

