#### Analysis Population, Missing Data, and Sensitivity Analyses

The primary analysis will follow the intention-to-treat principle, in which all participants will be analyzed in the groups to which their hospital was allocated, regardless of their level of app use, exposure to the leaflets, or subsequent adherence. Every effort will be made to obtain outcome data at 1 and 3 months for all enrolled caregivers, including those who discontinue or reduce use of the intervention [49].

Missing outcome data will initially be handled within the GEE framework, which uses all available repeated measurements under a missing-at-random assumption and provides robust standard errors. Patterns and reasons for missing data will be described. If more than a small proportion of outcome data (>20%) is missing, multiple imputation by chained equations will be considered as a sensitivity analysis, with covariates and outcome scores imputed under the missing-at-random assumption. Results from imputed and complete-case analyses will be compared to assess the robustness of the findings [21].

This study was conducted without any specific external financial support or grants from any public, commercial, or not-for-profit funding agencies. Recruitment and baseline data collection are currently underway at the time of manuscript submission (phase 1: 210 participants, phase 2 not yet started at the time of submission). The study findings are expected to be published in December 2026.

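### The SDs behind the 80% power look small for a 21-item right/wrong knowledge scale unless caregivers already score high; check them against Phase 1 data and restate the power

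*Protocol article*

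**What the plan says.** The Protocol article, Sample Size Calculation, compares two independent means, "assuming equal group sizes, a 2-sided test with a significance level of" 0.05 and 80% power. The inputs come from one cited study: "an expected mean difference in knowledge scores of 1.69 was used, with SDs of 2.53 and 2.76, respectively". The result is 38.5 ("Thus, approximately 39 participants are required per group"), inflated to 50 recruited per arm. The section does not state the instrument, population or mean score behind these values.

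Under Study Outcome, Knowledge, the outcome is the 21-item DKAT-2. "Each item is scored as correct or incorrect", and a don't-know answer counts as incorrect. Citing the scale's development study, the article credits it with "strong psychometric performance, including high internal consistency (Cronbach *α*=0.79". Under Results, Reliability, it sets 0.70 as the lowest acceptable alpha for the Malay version.

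The article gives no expected mean score. The Introduction and Principal Findings describe low or average knowledge among dementia caregivers.

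Phase 1 gives the same scale to a target of 363 caregivers from December 2024 to July 2025. Phase 2 recruitment starts in August 2025. The status at submission was "phase 1: 210 participants, phase 2 not yet started at the time of submission".

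**The concern.** The spread of a sum of right/wrong items is tied to how hard the items are and how strongly they hang together. SDs from an outside study can therefore be checked against the scale the trial will use. Here they look small for 21 binary items with alpha 0.79, unless most caregivers already answer most items correctly. That fits poorly with a trial motivated by gaps in knowledge, and it would leave limited room for a 1.69-point gain.

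If the SD in this population is larger, the printed power is too favourable, and a non-significant knowledge result could be read as absence of effect when the trial had limited ability to show one. Phase 1 yields the needed SD before Phase 2 opens, but the article does not describe using it.

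**Working it through.** **1. The plan's figure reproduces.** Inputs from Sample Size Calculation: SDs 2.53 and 2.76, difference 1.69, z-values 1.96 and 0.842.

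n = (2.53² + 2.76²)(1.96 + 0.842)² / 1.69² = 14.0185 × 7.8512 / 2.8561 = 38.54, so 39 per group.

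Pooled SD = √(14.0185/2) = 2.647. Standardised difference = 1.69/2.647 = 0.638. Power at 39 per arm is 80.5% by the normal approximation and 79.5% by the t test. There is no arithmetic error.

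**2. What that SD implies on this scale.** For right/wrong items Cronbach alpha equals KR-20:

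alpha = (k/(k−1)) × (1 − Σpq/SD²), with k = 21, p the proportion correct on an item and q = 1 − p. Hence Σpq = SD² × (1 − alpha × 20/21).

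- alpha 0.79: factor 0.2476; Σpq = 7.009 × 0.2476 = 1.736; mean pq = 0.0826.
- alpha 0.70: factor 0.3333; Σpq = 2.336; mean pq = 0.1113.

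With P the mean proportion correct and s the SD of item difficulty, mean pq = P(1 − P) − s². Solving for the mean score 21P, with s assumed:

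| s | alpha 0.79 | alpha 0.70 |
|---|---|---|
| 0 | 19.1 | 18.3 |
| 0.10 | 18.8 | 18.0 |
| 0.20 | 18.0 | 17.1 |
| 0.25 | 17.3 | 16.3 |
| 0.30 | 16.3 | 15.1 |

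For s from 0 to 0.25 the implied mean is about 17 to 19 (alpha 0.79) or 16 to 18 (alpha 0.70). At alpha 0.79 the room left below 21 is about 2 to 4 points. A mean of 60-70% correct at alpha 0.79 would need s of about 0.36 to 0.40.

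**3. The SD if knowledge is lower.** Assume P from 0.60 to 0.80 and s from 0.15 to 0.20. Then SD = √(21 × mean pq / factor). Power is for 1.69 points by t test, two-sided 0.05, 39 per arm, unadjusted.

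| P | s | mean pq | SD (alpha 0.79) | power | SD (alpha 0.70) | power |
|---|---|---|---|---|---|---|
| 0.60 | 0.15 | 0.2175 | 4.30 | 40% | 3.70 | 51% |
| 0.70 | 0.20 | 0.1700 | 3.80 | 49% | 3.27 | 62% |
| 0.80 | 0.20 | 0.1200 | 3.19 | 64% | 2.75 | 76% |

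The difference detectable with 80% power at 39 per arm is 2.802 × SD × √(2/39): 2.02 to 2.73 points over the alpha 0.79 range and 1.74 to 2.35 over the alpha 0.70 range.

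**4. Effect of baseline adjustment.** The analysis section includes the baseline score as a covariate. As an approximation, the residual SD is SD × √(1 − r²), where r is the baseline-to-follow-up correlation (not stated; assumed here). Over SD 3.19 to 4.30, power is 76% to 51% at r = 0.5, 82% to 57% at r = 0.6, and 90% to 67% at r = 0.7. Regaining the planned residual SD of 2.647 needs r = √(1 − (2.647/SD)²): 0.56 at SD 3.19 and 0.79 at SD 4.30.

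**5. Precision of a Phase 1 SD.** With 210 caregivers the relative standard error of an SD is about 1/√(2 × 209) = 4.9% (normal approximation).

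**The case against.** A reader might infer that the SDs are possible only if caregivers score near the ceiling. The documents do not support that. Alpha and the SDs come from different studies, and alpha belongs to a sample rather than to an instrument. At alpha 0.79, seven items at 10% correct and fourteen at 90% give a mean of 13.3 with SD 2.76. At alpha 0.60, SD 2.65 fits means of 14.9 to 17.4 for s up to 0.25. These escapes are real but costly: the first needs very uneven items, and an alpha of 0.60 would fail the plan's own 0.70 threshold.

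A reader might also infer that the stated power is probably far too high. That would need a mean score the article never gives. The surveys cited in the Introduction are from China and India, and no DKAT-2 mean is given for Malaysian clinic caregivers. It would also ignore the baseline adjustment, which at a correlation of 0.6 to 0.7 could recover much of the loss. This objection stands, with one limit: the printed 80% is an unadjusted two-sample figure and claims no such gain.

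Finally, if the outside study used another scale, the 1.69 would change along with the SDs, and the standardised effect could move either way. That is correct. It weakens any claim about direction, but it is also a reason to name the scale.

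**Conclusion.** The sample-size arithmetic is right. What is weak is the match between the planning SDs and the outcome. Under ordinary item spread they imply about 17 to 19 of 21 correct at alpha 0.79, or 16 to 18 at alpha 0.70, in tension with the article's account of caregiver knowledge.

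If caregivers score 60-80% correct, unadjusted power at 39 per arm could be about 40-64% (alpha 0.79) or 51-76% (alpha 0.70) rather than 80%. This rests on assumed mean scores and item spread, a 1.69-point difference held fixed, and no credit for baseline adjustment. The documents support saying that the power could be overstated and should be checked. They do not establish that it is overstated, or that the passages strictly contradict each other.

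**What to change.** Before Phase 2 opens, compute the mean and SD of the DKAT-2 total score in the Phase 1 sample, on the item set that Phase 2 will use. In Sample Size Calculation:

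- Replace 2.53 and 2.76 with that SD, and restate the unadjusted power for 1.69 points, or the difference detectable with 80% power, at the planned size (39 evaluable, 50 recruited per arm).
- State any gain from baseline adjustment separately, with the correlation it assumes.
- Name the knowledge scale from which the 1.69 and the borrowed SDs come.
- If the Phase 1 mean lies within about 2 to 3 points of 21, say that a ceiling limits the gain that can be shown.

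Keep the enrolment target. The cost is one calculation on data Phase 1 already collects and a few sentences of text. The downside is that the stated power may become less favourable.
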